##### Structural MRI (sMRI) and voxel-based morphometry (VBM)

2.6.2.1

PD is associated with widespread cortical gray matter atrophy (e.g., frontal lobe, cingulate cortex), where reduced gray matter volume is correlated with cognitive decline (30). sMRI involves automated whole-brain analysis to assess the characteristics of gray matter, white matter, and cerebrospinal fluid. VBM, as a method of sMRI image processing, aids in differential diagnosis, and monitoring disease progression (31). The imaging parameters were standardized as follows: T1WI will be acquired using a 3D MPRAGE sequence (TR/TE/TI = 2,300/2.98/900 ms, flip angle = 9°, voxel size = 1 × 1 × 1 mm3, 176 sagittal slices, acquisition time approximately 5–6 min). T2WI will be acquired using a 2D turbo spin-echo sequence (TR/TE = 3,650/92 ms, slice thickness/gap = 5/1.5 mm). T2-FLAIR will be acquired using a 2D sequence (TR/TE/TI = 9,000/120/2,500 ms, slice thickness/gap = 5/1.5 mm).

##### Resting-state fMRI (rs-fMRI)

2.6.2.1

rs-fMRI leverages blood oxygen level-dependent (BOLD) signals to map spontaneous neural activity and functional connectivity, capturing neurovascular uncoupling patterns in PD (32). Aberrant connectivity within the basal ganglia-thalamocortical circuit and dysregulation of posterior cortical regions, the caudate, and the cerebellum have been mechanistically linked to both motor and non-motor symptoms (33). These insights advance the understanding of PD pathophysiology and inform therapeutic development. Imaging Protocol: simultaneous multislice (SMS) BOLD sequence (multiband factor = 4): TR/TE = 500/30 ms, field of view = 224 × 224 mm^2^, voxel size = 3.5 × 3.5 × 3.5 mm3, 35 axial slices, 960 volumes, acquisition time = 8 min. Participants will be instructed to keep their eyes closed, remain still, and stay awake.

##### Diffusion tensor imaging (DTI)

2.6.2.3

DTI quantifies microstructural integrity and evaluates the microstructural integrity of nigrostriatal pathways through water diffusion anisotropy (34). Reduced fractional anisotropy (FA) in the substantia nigra, putamen, and caudate reflects dopaminergic degeneration, serving as an early biomarker for connectivity disruption and disease progression (35). Imaging Protocol: SMS-DTI sequence: TR/TE = 4,200/72 ms, ST/SG = 2/1 mm, voxel size = 2 mm3, 99 diffusion directions, b-values = 0–3,000 s/mm^2^ (gradient distributions: 0, 300, 350, 650, 950, 1,000, 1,350, 1,650, 1,700, 2,000, 2,700, 3,000).

##### Susceptibility-Weighted Imaging (SWI) and Neuromelanin MRI (NM-MRI)

2.6.2.4

In PD, iron accumulation in nigrosome-1 and neuromelanin depletion in the substantia nigra pars compacta (SNc) are pathognomonic (36). SWI detects iron deposition via phase-sensitive contrast (37), whereas NM-MRI tracks neuromelanin loss through T1-shortening effects (38), offering high diagnostic specificity for early PD detection. Imaging protocols: SWI will be acquired using a 3D flow-compensated gradient-echo (GRE) sequence, saving both magnitude and phase images (TR/TE = 27/20 ms, flip angle = 15°, voxel size = 1 × 1 × 1 mm3, slice thickness = 1 mm, acquisition time ≈ 5–7 min). NM-MRI will be acquired using a T1-weighted turbo spin-echo sequence (TR/TE = 600/13 ms, slice thickness = 2.5 mm, field of view = 220 × 220 mm^2^, acquisition time ≈ 8 min).

#### Others

2.6.3

##### Medication monitoring

2.6.3.1

During the observation period, participants will maintain a standardized PD diary to document all concomitant medications and healthcare resource utilization aimed at managing PD symptoms. Diary entries will be cross-verified with electronic medical records during follow-up visits to ensure accuracy and completeness.

##### Acupuncture expectancy assessment

2.6.3.2

Prior to the first intervention, participants will complete the validated Patients' Expectancy Scale of Acupuncture (PESA) (39), an 11-item instrument evaluating four domains: disease-related expectations, treatment-related beliefs, process-related concerns, and outcome-related projections. Responses are recorded on a 10-point Likert scale (1 = strongly disagree to 10 = strongly agree). Total scores will be analyzed as covariates to assess expectancy effects on therapeutic outcomes.

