**Figure 1 F1:**
[figure not shown]
Trial flow chart. PD, Parkinson's disease; VA, Verum acupuncture; SA, sham acupuncture; HCs, healthy controls; MRI, magnetic resonance imaging; AE, adverse events; SAE, serious adverse events.

**Table 1 T1:** Time points of treatment assessment.

Time point	Enrollment	Baseline	Treatment		Follow-up
	Week 1	Week 0	Week 2	Week 4	Week 8
Screening and enrollment					
Clinical interview	×				
Laboratory test	×			×	
Eligibility screen	×				
Informed consent	×				
Randomization		×			
Interventions					
Acupuncture			Eight sessions treatment + basic treatment		
Sham acupuncture			Eight sessions treatment + basic treatment		
Waiting-list			Basic treatment		
Assessments					
UPDRS-III		×		×	×
MDS-NMSS		×		×	×
PDQ-39		×		×	×
Footscan		×		×	
Synapsys		×		×	
SWE		×		×	
Multimodal MRI		×		×	
Others					
AEs, SAEs			×	×	×
Blinding assessment			×^*^	×	
PESA		×			
Patient compliance				×	×
Deqi sensation assessment^**^			×	×	
Medication adherence		×	×	×	×

^*^Assessed after the first and fourth session of acupuncture treatment.

^**^Assessed immediately after each acupuncture treatment.

UPDRS-III, Parkinson's Disease Rating Scale part III motor examination; NNMS, Parkinson's Disease Non-motor Symptom Scale; PDQ-39, 39-item Parkinson's Disease Questionnaire; SWE, shear wave elastic imaging; MRI, magnetic resonance imaging; AE, adverse events; SAE, serious adverse events; PESA, patients expectation scale of acupuncture.

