### Randomization, allocation, concealment and blinding

2.4

Randomization will be generated with the use of a random-number method via a computerized central randomization system. Eligible PD patients will be allocated in a 1:1:1 ratio to three groups: verum acupuncture, sham acupuncture, or waitlist control. After confirming eligibility, investigators will request group assignment via the centralized system, which automatically assigns and communicates the allocation to the investigator for intervention implementation. The randomization sequence will remain concealed on a secure server until completion of participant enrollment, data collection, and analysis to prevent selection bias.

To ensure methodological rigor, blinding will be implemented between the verum and sham acupuncture groups via a sham placebo acupuncture device (SPAD; Patent No. 2023215153288). The participants in both groups will receive treatments in private rooms to prevent cross-group communication. Outcome assessors, independent third-party personnel blinded to group allocations, will conduct all the clinical evaluations. A primary blinding code will be applied to the statistical database, ensuring that statisticians remain unaware of group assignments during analysis.

Owing to the inherent nature of acupuncture interventions, full blinding between acupuncture groups (verum/sham) and the wait-list control group is unattainable. However, stringent separation of study phases (recruitment, intervention, assessment) and adherence to predefined standard operating procedures (SOPs) minimize bias risks. In cases of serious adverse events (SAEs) requiring urgent unblinding (e.g., life-threatening complications), the principal investigator will access the allocation code via a sealed envelope stored in a secure location, document the reason, and report to the ethics committee within 24 h. Post-trial, the success of participant blinding will be evaluated via structured questionnaires. If blinding is compromised, we will perform sensitivity analyses by including blinding success as a covariate in the primary outcome models to assess its impact on treatment effect estimates.

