### Intervention

2.5

All PD participants will receive eight sessions (twice weekly for 4 weeks) of either verum or sham acupuncture. The regimen was derived from our clinical practice and informed by a pilot study that demonstrated significant clinical improvements, with due consideration of the need to balance treatment intensity and participant burden. The wait-list control group will receive no acupuncture during the observation period but will be offered the intervention post-trial. Patients on antiparkinsonian medications (e.g., levodopa) will maintain their regimen, with levodopa equivalent doses (LED) calculated at baseline. During the trial, medication adjustments are strongly discouraged; however, if any adjustment becomes clinically necessary, the change will be fully documented in case report forms (CRFs). HCs will undergo baseline MRI only, without interventions.

The verum and sham acupuncture groups will utilize the SPAD to ensure participant blinding. After standard skin disinfection, the SPAD is affixed to the target acupoint. For verum acupuncture, a sharp needle is inserted through the SPAD base to penetrate the skin. For sham acupuncture, a blunt-tip needle retracts upon contact with the skin, whereas microneedles within the SPAD simulate tactile penetration, replicating the deqi sensation without actual insertion. Figure 2 illustrates the blinding setup.

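### The expectancy score (PESA) is timed before the first treatment rather than before randomisation, so a covariate for wait-list contrasts may be collected after the allocation is known

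*Protocol article*

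**What the plan says.** All references are to the protocol article.

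- **Timing of PESA.** Section 2.6.3.2: "Prior to the first intervention, participants will complete the validated Patients' Expectancy Scale of Acupuncture (PESA"). Randomisation is not mentioned. The domains include beliefs about the treatment and forecasts of its result.
- **Use of the score.** The same section: "Total scores will be analyzed as covariates to assess expectancy effects on therapeutic outcomes". This is not limited to the two needled arms.
- **Trigger for assignment.** Section 2.4: "After confirming eligibility, investigators will request group assignment via the centralized system". The system then "automatically assigns and communicates the allocation to the investigator for intervention implementation". Completed baseline assessments are not named as a condition.
- **Visit schedule.** Table 1 puts the eligibility screen in the enrolment column. Randomisation and PESA are both in the Baseline, Week 0 column, with no order between them.
- **Wait-list arm.** Section 2.4 concedes that "full blinding between acupuncture groups (verum/sham) and the wait-list control group is unattainable". Section 2.5: "The wait-list control group will receive no acupuncture during the observation period but will be offered the intervention post-trial".
- **Main covariate model.** The ANCOVA in section 2.9.1 adjusts for the baseline score, age, duration of disease and levodopa-equivalent dose. PESA is not on that list.

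**The concern.** Adjusting a randomised comparison for a covariate is safe when allocation cannot have influenced the covariate. Completion before randomisation guarantees that; completion before treatment does not, because allocation is issued before treatment starts.

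The distinction matters for this scale and this control arm. PESA asks what the patient expects from acupuncture, and a wait-list patient who has been told that none will be given during the 8-week observation period may well answer differently. The score then partly measures the arm. Putting it in a model that compares verum or sham with wait-list credits some of the arm difference to expectancy, and the estimated expectancy effect becomes mixed up with allocation.

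The discussion relies on the wait-list arm to separate specific from non-specific effects, and that is the comparison in which an expectancy adjustment would be read most closely.

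**Working it through.** **Step 1: does any passage fix the order?** The plan gives no figure to reproduce here, so the passages are set side by side.

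| Question | Source | Answer |
|---|---|---|
| What must PESA precede? | 2.6.3.2 | The first intervention |
| What must assignment follow? | 2.4 | Confirmation of eligibility |
| When is eligibility screened? | Table 1 | Enrolment, before Week 0 |
| When are randomisation and PESA? | Table 1 | Both Week 0, order not given |
| Is wait-list blinded? | 2.4 | No |
| First acupuncture session for wait-list? | 2.5, 2.5.3 | Only after the trial |

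The sequence eligibility, assignment, PESA, first session meets every stated rule. So does eligibility, PESA, assignment, first session. The plan allows both, and only the second protects the covariate. For wait-list patients the anchor in 2.6.3.2 has no acupuncture session within the trial to refer to.

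**Step 2: size of the bias if PESA is collected late.** Let d be the amount by which knowing the allocation lowers mean wait-list PESA, in within-arm SDs, and r the within-arm correlation of PESA with improvement. The adjusted contrast is the unadjusted contrast minus slope × (difference in mean PESA). In SD units the slope is r and the difference is d, so the contrast with wait-list moves by about r × d, towards a smaller advantage over wait-list when r is positive.

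Assumed ranges, not in the documents: r 0.2 to 0.4, d 0.3 to 0.8.

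- Lower end: 0.2 × 0.3 = 0.06 SD
- Upper end: 0.4 × 0.8 = 0.32 SD

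**Step 3: in UPDRS-III points, for sham versus wait-list.** Section 2.3 gives expected changes of 2.84 ± 3.08 (sham) and 2.3 ± 3.0 (wait-list).

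- Pooled SD = √((3.08² + 3.0²)/2) = √(18.4864/2) = 3.04
- Bias = 0.06 × 3.04 = 0.18 to 0.32 × 3.04 = 0.97 points
- Expected difference = 2.84 − 2.3 = 0.54 points, or 0.54/3.04 = 0.18 SD
- The bias equals the expected difference when r × d = 0.18. At r = 0.4 that needs d of about 0.44. At r = 0.2 it needs about 0.89, which is outside the assumed range.

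**Step 4: simulation check.** Settings: 23 per arm, 4,000 replicates, true verum minus wait-list effect 1.0 SD (assumed), ANCOVA with PESA as covariate.

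| Shift d | r = 0.2: adjusted effect (SE) | r = 0.4: adjusted effect (SE) |
|---|---|---|
| 0 | 1.00 (0.290) | 1.00 (0.271) |
| 0.5 | 0.90 (0.296) | 0.80 (0.278) |
| 1.0 | 0.81 (0.314) | 0.59 (0.294) |

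The results follow 1 − r × d. With no shift, which is what completion before randomisation secures, there is no bias.

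**The case against.** The strongest reply is that this is silence rather than error. Table 1 lists PESA at baseline, ahead of every treatment column. The order of tasks within one visit is often left to procedures outside an article, and section 2.4 refers to such procedures. That section also says the allocation goes to the investigator; it does not say when the patient is told. This reply stands in part: a reader might infer that the plan prescribes PESA after allocation, and it does not. But the article does more than stay silent. It states a timing rule and an analytic use for the score, and the rule does not protect the use.

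Three further inferences go beyond the text.

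- **That the main clinical model is affected.** Section 2.9.1 does not list PESA, and section 2.6.1 makes all clinical outcomes exploratory, with MRI as the primary endpoint.
- **That PDQ-39, NMSS, UPDRS-III and baseline MRI share the fault.** They appear in Table 1 simply as baseline measures. The treatment-anchored wording of 2.6.3.2 does not apply to them, and clinical evaluations are made by blinded assessors.
- **That the bias is 0.4 to 2.0 points.** This follows from pooling all three SDs: √((9.94² + 3.08² + 3.0²)/3) = 6.25. That figure is dominated by the verum SD and is out of scale with a sham minus wait-list difference. A three-arm common-slope model could make a larger SD relevant, but the plan specifies no such model.

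It is also fair to say that expectancy questions keep some meaning for wait-list patients, who are offered acupuncture afterwards. Their answers may then refer to a different, later treatment.

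**Conclusion.** The point holds as a badly chosen timing anchor. The plan permits an expectancy covariate to be collected after a wait-list patient knows the allocation, and it does not restrict the covariate to the arms where that would do little harm.

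The exposed analysis is the exploratory expectancy analysis of section 2.6.3.2, in contrasts with wait-list. Verum versus sham is largely unaffected, because patients in both arms expect needling and are blinded to its type.

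If PESA is collected late, the bias is about r × d: 0.06 to 0.32 SD, or roughly 0.2 to 1.0 UPDRS-III points for sham versus wait-list, against an expected difference of 0.54. Both r and d are assumptions, so the range shows what could happen and is not an estimate. For proportion, the standard error of that contrast with 23 per arm is about 3.04 × √(2/23) = 0.90 points. The upper end of the bias is thus about one standard error, in a comparison that is already imprecise.

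**What to change.** In section 2.6.3.2, replace the treatment anchor with completion after consent and before randomisation, in all three arms. In Table 1, show PESA ahead of randomisation within Week 0. In section 2.4, make a completed PESA a condition for requesting assignment.

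If that order cannot be guaranteed, including for patients already enrolled, state that PESA will be a covariate only in the verum versus sham comparison.

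The cost is one phrase, a reordered table row and a check at the assignment step. No new visit, instrument or data item is needed. The change is worth making before data collection, because later analysis cannot reliably recover what a patient would have answered before learning the allocation.

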##### Blinding assessment

2.6.3.3

To evaluate blinding success, participants in the verum and sham acupuncture groups will complete a post-intervention questionnaire after their first, fourth, and final sessions. The assessment comprises the following: (1) treatment type guess: “Which intervention do you believe you received?” (Options: traditional acupuncture, acupuncture-like stimulation, uncertain). (2) Treatment preference confidence: a 10-cm visual analog scale (VAS) anchored by sham acupuncture (0 cm) and verum acupuncture (10 cm) was used.

##### Deqi sensation assessment

2.6.3.3

To objectively assess deqi sensation, patients will rate its intensity immediately after each session on a 10-cm visual analog scale (VAS), anchored with 0 = “no sensation” and 10 = “unbearable sensation”.

##### Patient compliance assessment

2.6.3.4

Patient compliance will be recorded at the end of the treatment. Dropouts and reasons will be documented during the 8-week observation period.

### Safety assessments

2.7

All adverse events (AEs), including symptom severity, onset time, interventions, outcomes, and follow-up details, will be documented in CRFs. For SAEs leading to participant withdrawal, a dedicated withdrawal form will record the reason, last treatment date, completed assessments, and SAE resolution status. All SAEs will be reported promptly to the institutional review board, principal investigator, and trial coordinator. AE causality will be assessed, and all events will be monitored until resolution or stabilization. Reporting will adhere to CONSORT guidelines for non-pharmacological trials.

### Data management and quality control

2.8

Prior to study initiation, all personnel will undergo standardized training on protocol adherence, outcome measurement protocols, and eligibility criteria. Clinical data will be systematically recorded in CRFs with built-in validation checks and stored securely. Data access will be restricted to authorized personnel until study completion to prevent premature analysis bias. The quality assurance (QA) team will perform bimonthly audits, evaluating protocol compliance, data accuracy, and procedural consistency. Licensed acupuncturists must hold ≥2 years of specialized training in the QNT, verified through competency assessments. To ensure consistency of the acupuncture technique across practitioners, all acupuncturists will undergo a standardized training session and pass a practical examination before the trial commences. During the trial, procedural checklists will be used for each treatment session, and video recordings of a random 10% of sessions will be reviewed by an independent expert to verify adherence to the standardized manipulation protocol. Any deviations will be discussed in regular team meetings to maintain treatment fidelity. All scans will be acquired on a single Siemens Prisma 3.0T scanner (64-channel head coil) at the First Affiliated Hospital of Guangzhou University of Chinese Medicine, operated by two certified MRI technicians.

An independent Data Monitoring Committee (DMC) comprising a neurologist, a statistician, and an acupuncture therapy expert will be established. The DMC will review interim safety data every three months, assess trial conduct, and recommend continuation or termination on the basis of predefined stopping rules (e.g., SAE rate exceeding 10%). The DMC operates independently from the sponsor and investigators, with all communications documented in meeting minutes. As this is a mechanistic trial with neuroimaging as the primary endpoint, no interim efficacy or futility analysis is planned, as early termination for efficacy would preclude adequate collection of neuroplasticity data.

### Statistical analysis

2.9

#### Clinical data analysis

2.9.1

All statistical tests will be two-tailed, with significance set at α = 0.05. Baseline demographic and clinical characteristics will be summarized descriptively by group. Baseline demographic and clinical characteristics will be summarized descriptively by group. To assess baseline comparability among the three randomized groups, one-way ANOVA (or Kruskal–Wallis test) will be used for continuous variables, and chi-square tests for categorical variables. If significant between-group differences are observed at baseline, the affected variables will be included as covariates in subsequent analyses to adjust for potential confounding. For the primary clinical outcome, no correction for multiple comparisons is applied as this is a single predefined comparison. For secondary clinical outcomes, we will apply False Discovery Rate (FDR) correction within each assessment scale. Continuous data will be analyzed via one-way ANOVA (normally distributed data) or the Kruskal–Wallis *H*-test (non-normal data), with Bonferroni-adjusted *post-hoc* comparisons. Categorical variables will be analyzed using the Pearson χ^2^ test or Fisher's exact test for unordered variables, and the linear trend χ^2^ test for ordered variables. Analysis of covariance (ANCOVA) will be employed to adjust for baseline values, age, disease duration, and levodopa equivalent daily dose where appropriate. If significant baseline differences between groups are observed after randomization, these variables will be included as covariates in the corresponding models to mitigate bias. Missing data will be handled using multiple imputation by chained equations under the missing at random assumption, with sensitivity analyses comparing imputed results to complete-case analyses. An intention-to-treat (ITT) analysis will include all randomized participants, whereas per-protocol analyses will exclude non-compliant cases (< 80% session attendance).

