#### Clinical outcomes

2.6.1

This trial is primarily designed to detect neuroplastic changes via multimodal MRI. Accordingly, the primary endpoint is the change in multimodal MRI biomarkers, whereas all clinical outcomes and biomechanical indices are designated as exploratory endpoints.

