##### Unified Parkinson's Disease Rating Scale part III (UPDRS-III)

2.6.1.1

Although all clinical analyses are exploratory, the change in UPDRS-III total score from baseline to week 4 is designated as the primary clinical outcome measure to maintain temporal alignment with the primary neuroimaging assessments. The UPDRS, revised by the Movement Disorder Society (MDS) in 2008 (20), is the gold standard for comprehensive PD symptom assessment (21). The Chinese version of the PD scale has excellent reliability and validity in Chinese PD patients (22). The UPDRS-III evaluates motor function via 18 items scored from 0–4 (higher scores indicate greater impairment). Assessments will occur at baseline, week 4 (post-treatment), and week 8 (end of follow-up; Table 1).

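### The model for the exploratory clinical outcomes is left to baseline significance tests and an undefined qualifier; one prespecified baseline-adjusted ANCOVA would fix it for a modest gain in precision

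*Protocol article*

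**What the plan says.** Section 2.9.1 (Clinical data analysis) of the protocol article makes four statements that bear on the clinical model.

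- **Balance tests.** "To assess baseline comparability among the three randomized groups, one-way ANOVA (or Kruskal–Wallis test) will be used for continuous variables", with chi-square tests for categorical variables. The level is set by "All statistical tests will be two-tailed, with significance set at α = 0.05".
- **Covariates from those tests, stated twice.** First "If significant between-group differences are observed at baseline, the affected variables will be included as covariates in subsequent analyses to adjust for potential confounding", and later in the same paragraph "If significant baseline differences between groups are observed after randomization, these variables will be included as covariates in the corresponding models to mitigate bias".
- **Analysis of continuous outcomes.** "Continuous data will be analyzed via one-way ANOVA (normally distributed data", with Kruskal–Wallis when data are not normal. Neither adjusts for anything.
- **ANCOVA.** "Analysis of covariance (ANCOVA) will be employed to adjust for baseline values, age, disease duration, and levodopa equivalent daily dose where appropriate". No criterion says when it is appropriate.

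On the status of these outcomes, section 2.6.1 says that "all clinical outcomes and biomechanical indices are designated as exploratory endpoints", and section 2.6.1.1 says that "the change in UPDRS-III total score from baseline to week 4 is designated as the primary clinical outcome measure". Section 2.3 repeats that the clinical efficacy analyses are exploratory. Section 2.6.3.2 adds that expectancy scores will also serve as covariates.

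**The concern.** Section 2.4 describes central computerised randomisation, so baseline differences between arms arise by chance. A significance test on them tests a null hypothesis already known to be true, and its p-value says nothing about whether the variable predicts outcome. A covariate earns its place by prognostic strength, judged in advance. The reasons the protocol gives for its rule, confounding and bias, do not fit chance imbalance.

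The second difficulty is that no sentence says which model produces the UPDRS-III result. It could be unadjusted ANOVA, Kruskal–Wallis after a normality check, ANCOVA with the four named covariates, or any of these plus whatever the balance tests pick up. Section 2.9.1 treats the lead clinical outcome as one predefined comparison, but its model is not predefined. With about 20 evaluable patients per arm, Hoehn-Yahr stages 1 to 4 and ages 25 to 80, a sizeable imbalance in a prognostic variable can occur without reaching significance and then stay unadjusted. Section 2.3 says these results will inform larger trials, so the estimate should be reproducible and reasonably efficient.

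**Working it through.** **Inputs from the protocol article.** Section 2.3: at least 20 per group, 10% attrition, 69 enrolled; expected UPDRS-III changes with SDs 9.94 (verum), 3.08 (sham) and 3.0 (wait-list). Section 2.9.1: two-sided α = 0.05. **Not given, so assumed over a range:** the baseline to week-4 correlation r, the baseline SD, and the number k of baseline variables tested.

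**1. The plan's own figure.** 20/0.9 = 22.2, rounded up to 23 per group; 3 × 23 = 69. This reproduces.

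**2. How often the tests add a covariate by chance.** Each test is significant 5% of the time under correct randomisation. For k independent tests the chance of at least one is 1 − 0.95^k: 18.5% (k = 4), 22.6% (k = 5), 40.1% (k = 10).

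**3. Gain from ANCOVA with equal SDs.** Its variance relative to a change-score ANOVA is (1 − r²)/(2(1 − r)) = (1 + r)/2: 0.75, 0.85 and 0.90 for r = 0.5, 0.7 and 0.8.

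**4. What the significance rule does to that gain.** Simulation of three arms of 23, equal SD 10, verum–sham difference 6, 4,000 runs per setting. Change-score ANOVA with baseline added only if its balance test has p < 0.05 is compared with ANCOVA always.

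| r | Power, rule / always | SE, rule / always |
|---|---|---|
| 0.5 | 52% / 62% | 2.85 / 2.58 |
| 0.7 | 74% / 80% | 2.27 / 2.13 |
| 0.8 | 89% / 91% | 1.85 / 1.78 |

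The rule admits baseline in about 5% of runs, so it recovers almost none of the gain. With no true effect, its rejection rate was 4.5% to 5.0%.

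**5. The same question with the section 2.3 SDs.** Steps 3 and 4 need equal SDs and one common r. Suppose instead equal baseline and week-4 SDs of σ within arm, with σ from 10 to 15. The change variance is d² = 2σ²(1 − r), so r = 1 − d²/(2σ²).

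- Verum (d² = 98.80): r = 0.51 to 0.78.
- Sham (d² = 9.49) and wait-list (d² = 9.00): r = 0.95 to 0.98.

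The slope of change on baseline in each arm is r − 1. At σ = 10 the slopes are −0.494, −0.047 and −0.045, and the common slope is their mean, −0.195. The variance left in an arm with slope β under a common slope b is d² − 2bβσ² + b²σ²:

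- verum: 98.80 − 19.31 + 3.82 = 83.31
- sham: 9.49 − 1.85 + 3.82 = 11.45
- wait-list: 9.00 − 1.76 + 3.82 = 11.06

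Variance ratios, ANCOVA to change score:

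- verum vs sham: (83.31 + 11.45)/(98.80 + 9.49) = 0.88
- sham vs wait-list: (11.45 + 11.06)/(9.49 + 9.00) = 1.22

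At σ = 15 the same steps give 0.94 and 1.10. These are large-sample values. Estimating the slope from 20 per arm adds a little: simulation over σ = 10 to 15 gives about 0.89 to 0.95 for verum vs sham and 1.19 to 1.27 for sham vs wait-list. A repeat run moved the ends slightly, to 0.96 and to 1.17 and 1.29. With a separate slope per arm, that repeat gave 0.87 to 0.96 and 1.01 to 1.03.

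**6. Unequal SDs and a pooled error term.** The mean variance is (98.80 + 9.49 + 9.00)/3 = 39.10. Relative to the correct unadjusted standard error, a pooled one is √(2 × 39.10/108.29) = 0.85 for verum vs sham and √(2 × 39.10/18.49) = 2.06 for sham vs wait-list. The planned ANOVA has this problem already, and an ordinary ANCOVA would keep it.

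**The case against.** The best defence is that the rule touches only exploratory endpoints. The MRI primary endpoint is analysed under section 2.9.2, which contains no such rule. This stands.

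A reader might infer that baseline UPDRS-III is left out unless its balance test is significant. The text does not say so: the ANCOVA sentence names baseline value, age, disease duration and levodopa equivalent dose with no significance condition. The tests add to that list and do not replace it. What remains is that the closing qualifier of that sentence sets no criterion, whether it governs the covariates or the use of ANCOVA itself. A separate analysis plan might supply one, but the significance rule is stated outright in the article and is not merely deferred.

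It is also fair that a change score already removes part of a baseline difference, and that the rule adjusts for the largest imbalances.

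Two figures invite over-reading. The equal-SD formula at r = 0.5 to 0.8 could suggest that 10% to 25% of patients are wasted. The SDs in section 2.3 do not support that: under the assumptions of step 5, that range of r fits only the verum arm. The 40% chance of adding a covariate needs ten independent baseline variables. The article states no such number, and independence is implausible for UPDRS-III, NMSS, PDQ-39, disease duration and levodopa dose. It describes how unstable the model is, not how much harm follows.

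**Conclusion.** The point holds as a matter of precision and prespecification for exploratory outcomes. Selecting covariates by baseline p-values is a poor rule, it is stated twice, and the model for week-4 UPDRS-III change is not fixed.

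The size is modest. If σ is 10 to 15, baseline and week-4 SDs are equal within arm and the section 2.3 change SDs hold, always adjusting lowers the verum–sham variance by about 5% to 11%. At 20 per arm the change-score standard error is √(108.29/20) = 2.33, and a ratio of 0.89 brings it to 2.20. With a common slope, the sham versus wait-list variance rises by about 20% to 27%. That contrast starts from a standard error of √(18.49/20) = 0.96, so a ratio of 1.27 gives 1.08. If the SDs prove equal across arms, the gain is larger and follows (1 + r)/2.

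Two stronger conclusions should not be drawn. The rule does not inflate type I error: the simulated rate stayed at 4.5% to 5.0%. Nor is adjustment free of any cost, as the sham versus wait-list contrast shows.

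**What to change.** - For UPDRS-III and the other continuous clinical outcomes, prespecify one ANCOVA: the outcome on arm and its own baseline value, plus a short fixed list drawn from age, disease duration and levodopa equivalent dose. Baseline only, or baseline with one or two of these, is defensible at about 20 per arm; what matters is that the list is fixed.
- Remove the qualifier that leaves ANCOVA to judgement, and say that this model gives the reported result.
- Because section 2.3 expects unequal SDs, use heteroscedasticity-robust standard errors with a small-sample correction, or arm-specific baseline slopes. Robust errors make the stated uncertainty honest. Arm-specific slopes also remove most of the precision loss for sham versus wait-list.
- Delete the baseline significance tests and both sentences that add covariates from them. Keep the baseline table descriptive.
- Keep the rank-based analysis as a sensitivity analysis, not as an alternative chosen by a normality check.

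The change is to wording, and baseline UPDRS-III and levodopa equivalent dose are already scheduled for collection. The cost is a few degrees of freedom and, under a common slope, possibly somewhat lower precision for sham versus wait-list.
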